##### Secondary

• ICU and HDU length of stay and acute hospital length of stay

• Days of antibiotic usage;

• Duration of PN usage;

• Alive, ventilator-free days as recommended by Rubenfield [26];

• Change in SOFA scores;

• Serious Adverse events (excluding deaths) (for reporting of Suspected Serio-s Adverse Reactions (SSARs) and Suspected Unexpected Serious Adverse Reactions (SUSARs).

• Patient quality of life measured by SF12 and EQ5D; and

• Costs to the NHS, patients and carers/families; incremental cost per day in ICU saved and/or per quality adjusted life years (QALYs)

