### Data analysis

Analysis of dichotomous outcomes will be analysed using statistical tests such the Chi-squared test. Continuous measures will be analysed using t-tests (with transformation of data to Normality if appropriate), or non-parametric equivalents. A further analysis accounting for the inter-relationship between deaths and length of stay will be undertaken, akin to that described for ventilator-free days by Rubenfield [26] mentioned earlier. This, for example, would allow the apparently short length of stays associated with early deaths to be accounted for appropriately. A significance level of 2p < 0.05 will be considered as evidence of statistical significance for the primary outcomes. Confidence intervals will also be presented where appropriate. The economic analysis will incorporate sensitivity analysis, and confidence intervals will be constructed around stochastic cost data using techniques such as bootstrapping [27].

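### Antibiotic days stop at death, but the plan's death-adjusted analysis covers only length of stay, so a mortality difference would distort the antibiotic comparison

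*Protocol article*

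**What the plan says.** In the Protocol article, the list of secondary outcomes under Measures of outcome includes "Days of antibiotic usage" and "Duration of PN usage". Neither entry has a time window or a rule for patients who die. The same list defines the ventilation outcome so that survival is part of it: "Alive, ventilator-free days as recommended", with a cited source.

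The Data analysis section gives one general rule: "Continuous measures will be analysed using t-tests (with transformation of data to Normality if appropriate), or non-parametric equivalents". It then makes one addition: "A further analysis accounting for the inter-relationship between deaths and length of stay will be undertaken", modelled on the method for ventilator-free days. The reason given is that this "would allow the apparently short length of stays associated with early deaths to be accounted for appropriately".

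The Ground rules for the statistical analyses keep everyone randomised in the analysis. A patient who dies early therefore contributes whatever number of antibiotic days had built up by then.

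**The concern.** A count of antibiotic days is cut short by death in the same way as a length of stay. A patient who dies on day 3 can have at most three days of antibiotics after randomisation, and on the raw scale that looks like low use. The plan recognises this mechanism for length of stay and avoids it for ventilation by definition. It leaves antibiotic days under the general t-test or rank-test rule.

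What is at stake is the reading of a result that the trial has reason to care about. Mortality is a primary outcome and the Background hopes for a reduction. The Background also links antibiotic use to resistance and cost, and the Abstract names antibiotic usage among the secondary outcomes. If a supplement saved lives, the raw comparison would tend to show more antibiotic days on that arm. If it cost lives, the raw comparison would tend to show fewer. Both statements assume that the supplement does not itself change how long survivors need antibiotics; a real effect on need would add to the distortion or offset it.

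**Working it through.** The plan gives no mean, SD or target difference for antibiotic days, so there is no figure to reproduce. The reading of the text settles the direction. The calculation below only shows a plausible size.

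**Inputs from the Protocol article**
- Planned total 500 (Power calculation), so about 250 on each side of a factorial margin.
- ICU mortality 15–20% and hospital mortality 30% (Background).
- Mortality relative risk 0.75 for parenteral glutamine, 95% CI 0.52 to 1.07 (Systematic reviews).
- ICU stay of about 9 days, SD 7 (Power calculation).

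**Assumptions not in the article**
- SD of antibiotic days is 7, borrowed from ICU stay.
- Each death removes 5 to 7 antibiotic days.
- All deaths in the mortality figure used are early enough to cut the count short.
- The supplement has no effect on the need for antibiotics.
- Two-sided 5% test. The article states this level for the primary outcomes.

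**Formulas**
- Mortality gap = base mortality × (1 − 0.75).
- False difference = mortality gap × days lost per death.
- Standard error = 7 × √(2/250) = 0.626 days.
- With z = false difference / 0.626, chance of rejection = Φ(−1.96 + z) + Φ(−1.96 − z).

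| Base mortality | Gap (points) | Days lost per death | False difference (days) | z | Rejection |
|---|---|---|---|---|---|
| 15% | 3.75 | 5 | 0.19 | 0.30 | 6.0% |
| 15% | 3.75 | 7 | 0.26 | 0.42 | 7.0% |
| 20% | 5.0 | 5 | 0.25 | 0.40 | 6.8% |
| 20% | 5.0 | 7 | 0.35 | 0.56 | 8.6% |
| 30% | 7.5 | 5 | 0.38 | 0.60 | 9.2% |
| 30% | 7.5 | 7 | 0.53 | 0.84 | 13.4% |

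The range is therefore about 0.2 to 0.5 days, with 6% to 13% rejection against a nominal 5%.

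**Check by simulation.** This used a different model: gamma-distributed days needed (mean 9, SD 7), deaths cutting the count at a uniform time over 0–7 or 0–14 days, 250 per arm, 2,000 runs, and a t-test on the raw count.
- At 30% v 22.5% mortality, the arm with more deaths showed about 0.44 (0–7) or 0.32 (0–14) fewer days. It came out significantly lower in about 12% or 8% of trials, against 2.5% expected in that direction.
- At 20% v 15%, the fall was 0.31 or 0.23 days, in about 7% or 6% of trials.
- At equal mortality of 30%, there was no material shift and about 5% of trials rejected.
- With a 28-day count of days alive and antibiotic-free, scoring death as zero, the arm with more deaths was worse in every scenario with unequal mortality, by 0.9 to 1.9 days.

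The simulated falls imply a loss per death of 0.44/0.075 = 5.9 days and 0.32/0.075 = 4.3 days. The later the deaths, the nearer the bias lies to the lower end of the table, or just below it.

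**The case against.** The strongest objection is that the raw count is inferred. The outcome list gives short labels, the article condenses a fuller document, and detailed definitions may sit elsewhere. That is fair as a caution. But the article does not merely stay silent: it fixes the general test and names what receives death-adjusted treatment, and antibiotic days are not included. The words introducing the example in "This, for example, would allow the apparently short length of stays associated with early deaths to be accounted for appropriately" illustrate the benefit of an analysis of deaths and length of stay. They do not widen it to other outcomes.

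The second objection is that raw antibiotic days are a legitimate quantity. Resistance pressure and NHS cost depend on antibiotics actually given, including to patients who die, and a composite is partly driven by mortality, which is already a primary outcome. This stands. It means that the raw count should be kept. It does not make the raw count a safe basis for saying that a supplement reduces the need for antibiotics.

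Third, the size depends on borrowed and assumed inputs. The top of the range treats all of the 30% hospital mortality as early death; ICU mortality of 15–20% gives about 6% to 9%. The interval for the relative risk includes 1, and with no mortality difference there is no bias. This also stands.

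Fourth, mortality is reported as a primary outcome, so readers would see an imbalance. That warns them but does not correct the antibiotic estimate.

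A reader might also infer that "Duration of PN usage" has the same defect. The article does not say that shorter PN is better, and duration can be read as a measure of exposure, so early death cannot be said to look like a benefit there.

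**Conclusion.** The point holds for antibiotic days. As written, the comparison is open to truncation by death, a mechanism that the plan itself recognises for length of stay. The direction is secure whenever mortality differs and the need for antibiotics does not. The size, about 0.2 to 0.5 days and 6% to 13% false rejection, is illustrative. It rests on an SD of 7 taken from ICU stay, 5 to 7 days lost per death, a relative risk of 0.75 and base mortality of 15% to 30%.

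Three stronger readings are not supported:
- That the raw comparison is an error to be removed. It answers the consumption and cost questions.
- That the adjusted length-of-stay analysis must become the main one. The plan already commits to it as a further analysis, and its rank is a choice of estimand.
- That antibiotic usage is a key outcome, or that the plan already scores deaths as zero for ventilation. The article lists antibiotic usage among the secondary outcomes without ranking it, and for ventilator-free days it only cites a source.

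This is a moderate inconsistency in a secondary outcome and should be settled before unblinding.

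**What to change.** In Data analysis, extend the death-adjusted further analysis to antibiotic days. Two forms would serve: days alive and antibiotic-free over a fixed window from randomisation, with the window and the scoring of deaths written down; or a competing-risk analysis with death as the competing event. State that any claim of reduced antibiotic use rests on this analysis. Report raw antibiotic days by arm beside it for consumption and cost.

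Apply the same handling to PN duration only if a shorter duration is to be read as a benefit; otherwise label it as a description of exposure. Making the adjusted length-of-stay analysis the main one is optional.

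The cost is mainly wording. The article does not show that dated antibiotic use is recorded over a fixed window, so the case report form should be checked and the window set to what the data allow. The small downside is that the alive-and-free count partly reflects mortality, which is why the raw days should stay in the report.

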## Background

Intensive care unit (ICU) and subsequent hospital mortality in the UK remains high, with figures of 15–20% and 30% respectively [1]. The cost per ICU bed-day exceeds £1,100 based on a mean from all trusts in England and Wales [2]. In many countries, including the UK, provision of intensive care is inadequate to meet demand. Infections acquired on the ICU have been associated with a two to three fold increased risk of death [3], this is associated with both illness and drug related impairment of the patient's immune system. Multiple portals for infection include: tracheal tubes, nasogastric tubes, chest and abdominal drains, central venous, pulmonary arterial and urinary catheters, wounds, and infective loci present before admission to ICU. These infections increase mortality, morbidity, length-of-stay, antibiotic usage and costs of care. As a result 40–50% of patients on ICU are prescribed antibiotics at any one time [2]. Such concentrated antibiotic usage may contribute to ICU, hospital and even community antibiotic resistance, which is a major health care issue [2,4-6].

A European point prevalence study in ICUs showed that 66% of patients were receiving artificial nutritional support, 42% of whom were receiving either parenteral nutrition alone (23%) or parenteral combined with enteral nutrition (19%). [7].

Although the enteral feeding route is preferred to parenteral (reduced costs of administration and reduced risk of infective complications from the intravenous line), parenteral nutrition (PN) retains an important supportive role in the management of ICU patients, many of whom cannot be fed effectively by the enteral route because of gastro-intestinal dysfunction [8].

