#### 2. Descriptive information

• Under-nourished, normal or obese, based on subjective clinical assessment [23]

• Patient groups – medical, or surgical (including trauma))

• APACHE (Acute Physiology and Chronic Health Evaluation) II score

• SOFA (Sequential Organ Failure Assessment) score

• Severe sepsis or septic shock

• Antibiotics/anti-infectives on recruitment

This information will be sent to the Trial Office.

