### Treatment allocation

The existing central randomisation service (fully automated computerised telephone randomisation) in the Health Services Research Unit at the University of Aberdeen will be used to randomise patients. Recruiting staff will telephone the randomisation line and will be asked to key in details of identification and important prognostic factors (see below), when confirming eligibility and consent. Consent procedures will adhere to the 2003 Mental Health (Care and Treatment) (Scotland) Act. Random allocation to one of the four possible treatment combinations (see above) will be minimised on trial centre; age (<65 years or ≥ 65 years); sex; patient groups (medical or surgical (including trauma)); and, patient nutritional status (under-nourished, normal or obese – subjective clinical assessment [24]. A four digit number for that patient will be provided by the automated randomisation service, the research nurse accessing the randomisation service will then inform the centre pharmacy of this randomisation number. The trial office, based at the University of Aberdeen will have provided each pharmacy with a list of these random numbers linked to one of the four treatment allocations, thus maintaining the blinding of local investigators to the trial treatment. Figure 1 summarises these arrangements.

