### Analysis plans

#### Ground rules for the statistical analyses

The statistical analyses will be based on all people randomised, irrespective of subsequent compliance with nutritional support. The principal comparisons will be:

(i) all those randomised glutamine versus all those not allocated glutamine

(ii) all those randomised selenium versus all those not allocated selenium

(iii) all randomised glutamine and selenium versus all randomised glutamine alone versus all randomised selenium alone versus all randomised placebo

Evidence will be sought for an interaction between glutamine and selenium.

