### Power calculation

The primary endpoint for the trial is the proportion of patients acquiring infection(s) after starting trial PN. Systematic reviews indicate that the reduction in proportion of patients acquiring infections in previous trials ranged from approximately 50% in the control arm to 40% in the intervention arm. Removing Griffiths' glutamine trial [31,32] – which only reported infections in a post-hoc analysis – shows the effect may indeed be greater (from 50% in the control arm to 30% in the intervention arm). A plausible reduction to detect would be the midpoint of these two estimates (i.e. a reduction from 50% to 35%), hence 340 participants would be required to detect this size of difference (with 80% power and 2p < 0.05) [33].

Given the high mortality rates in critical care patients [1], we have allowed for potential loss of patients to follow-up over the six months (see below – this would primarily affect secondary outcomes such as quality of life measures). We have consequently inflated the sample size requirement by approximately 20%, thus plan to recruit 500 patients to the trial.

Based on routine data available from the Scottish Intensive Care Society (SICS) audit database, the average length of ICU stay for patients receiving PN is approximately 9 (SD 7) days. For a 2 day reduction in ICU stay to be detected, with 80% power and 2p < 0.05, a trial of approximately 400 patients would be required. As we do not expect any dropout from the trial prior to discharge, we are adequately powered to detect this level of change.

A trial with 500 patients would allow us to detect a quarter of a standard deviation (0.25SD) change in hospital length of stay with 80% power and 5% significance (assuming all data for length of stay are available).

A trial of 340 patients would have 80% power and 5% significance to detect differences in Quality of Life measures of approximately 0.33SD (a third of a standard deviation change) or 90% power to detect a 0.5SD change. Previous research in the behavioural field suggests that a 0.5SD change is the level of change that should be associated with a moderate change in quality of life measures [34,35]. As such we are well powered to detect meaningful changes in quality of life measures.

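### Antibiotic days are compared without adjustment for antibiotic use at entry, which is recorded but unused; this gives up some precision and leaves chance imbalance uncorrected

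*Protocol article*

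**What the plan says.** All references are to the protocol article.

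- Measures of outcome, Secondary: one of the listed outcomes is "Days of antibiotic usage".
- Data analysis: "Continuous measures will be analysed using t-tests (with transformation of data to Normality if appropriate), or non-parametric equivalents". No covariate is named. The only outcome-specific refinement in that section concerns deaths and length of stay.
- Information collected at trial entry, Descriptive information: the form records "Antibiotics/anti-infectives on recruitment".
- Treatment allocation: allocation "will be minimised on trial centre; age (<65 years or ≥ 65 years); sex; patient groups (medical or surgical (including trauma" and nutritional status. Antibiotic use at entry is not among the factors.
- Secondary sub-group analyses: the list covers nutritional status, patient group, age, severity scores and severe sepsis or septic shock. Entry antibiotic use is not on it.
- Background: "As a result 40–50% of patients on ICU are prescribed antibiotics at any one time". This describes ICU patients in general, not trial entrants.
- Ground rules for the statistical analyses: the first principal comparison is "all those randomised glutamine versus all those not allocated glutamine", with a matching one for selenium. Each sets about 250 patients against 250.

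**The concern.** A patient already on antibiotics at recruitment will probably accumulate a different number of antibiotic days from one who is not, whatever the allocation. If so, entry status explains part of the variation in the outcome. A t-test or rank test without covariates leaves that part in the error term.

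There are two consequences. The comparison has less power than the collected data would support. And because minimisation does not balance entry antibiotic use, the arms may differ on it by chance; the unadjusted estimate then moves with that difference and nothing in the planned analysis corrects it.

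The stake is modest. This is a secondary outcome, and no sample size statement in the article rests on it.

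**Working it through.** **1. Reproduce the plan's own figure.** No power statement is made for antibiotic days. The closest is in Power calculation: "A trial with 500 patients would allow us to detect a quarter of a standard deviation (0.25SD) change in hospital length of stay". The power given there is 80% and the significance level 5% (taken as two-sided). With 250 per arm, the standard error of a difference in means is √(2/250) = 0.0894 SD. Then 0.25/0.0894 = 2.795, and power = Φ(2.795 − 1.960) = 79.8%. The total N for exactly 80% is 504. The stated figure reproduces and serves as the reference.

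**2. Inputs for the adjustment.**
- p, the share on antibiotics at entry: 40–50%, from Background. It is a proxy, since the article gives no figure for entrants.
- D, the difference in mean antibiotic days between patients on and off antibiotics at entry, in outcome SDs: **an assumption**, taken from 0.25 to 1.0.

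**3. Formulas.** Share of variance explained: R² = p(1 − p)D². Residual SD after adjustment: √(1 − R²). Power: Φ(2.795/√(1 − R²) − 1.960). Equivalent number of patients: 500/(1 − R²).

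Example with p = 0.45 and D = 0.75: R² = 0.2475 × 0.5625 = 0.139; residual SD 0.928; power Φ(3.013 − 1.960) = 85.4%; 500/0.861 ≈ 581 patients.

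| D (assumed) | Variance removed, p = 40–50% | Power for 0.25 SD | 500 patients act like |
|---|---|---|---|
| none (unadjusted) | – | 79.8% | 500 |
| 0.25 | 1.5–1.6% | 80.4% | 508 |
| 0.50 | 6.0–6.2% | 82.2–82.3% | 532–533 |
| 0.75 | 13.5–14.1% | 85.2–85.4% | 578–582 |
| 1.00 | 24–25% | 89.4–89.8% | 658–667 |

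To put D in days, again as an assumption: with p = 0.45, a 4-day difference and a within-group SD of 5 days, R² = 0.2475 × 16/(25 + 0.2475 × 16) = 3.96/28.96 = 0.137. That is close to the D = 0.75 row.

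**4. Chance imbalance.** The standard error of the between-arm difference in entry antibiotic use is √(p(1 − p) × 2/250), or 4.4 to 4.5 percentage points. The 95% limit is 1.96 times that, or 8.6 to 8.8 points. An imbalance at that limit shifts the unadjusted difference by imbalance × D: 0.02 SD at D = 0.25 and 0.09 SD at D = 1.0, which is 0.24 to 0.98 of the standard error. This treats allocation as unrelated to entry antibiotic use.

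**5. Simulation.** 20,000 trials of 250 v 250, p = 0.45, D = 0.75, no treatment effect.
- Over all trials: the unadjusted estimate averaged 0.000 SD. Type I error was 5.3% unadjusted and 5.0% adjusted. The SD of the estimate was 0.0893 unadjusted and 0.0826 adjusted, a variance reduction of 1 − (0.0826/0.0893)² ≈ 14%, in line with step 3.
- In the 7.8% of trials with an imbalance above 8 points in either direction: type I error was 12.8% unadjusted and 4.8% adjusted. Imbalances above 8 points in one given direction shifted the estimate by 0.074 SD unadjusted and 0.001 SD adjusted.

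**The case against.** The strongest reply is that covariates for one secondary outcome belong in the statistical analysis plan, and that a condensed article's generic sentence on continuous outcomes should not be read as excluding them. This has force: a plan not shown may add covariates, and it may define the counting window for antibiotic days. The absence of a window is therefore not raised here. But the article does more than stay silent. It names the tests, and it adds special handling where its authors saw a need (deaths and length of stay). A recorded predictor left out of a stated method is a choice that can be improved.

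A second reply is that the comparison is valid as planned and that the same could be said of many outcomes and baseline variables. The first half is right. The second is weakened because the covariate here is the entry state of the very thing the outcome measures.

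A third is that the size rests on inputs the documents do not supply. That stands too. If entry status shifts the outcome by only 0.25 SD, the gain is about 1.5% of the variance and half a point of power.

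Three stronger readings are tempting, and the documents do not support them:
- *That the result is biased.* On average it is not. The shift appears only conditionally, in a trial where a sizeable imbalance has occurred.
- *That much of the antibiotic use counted after entry is the tail of courses begun earlier.* A figure for how many are on antibiotics at one moment says nothing about how long those courses still have to run, or about their share of a total over an unstated window.
- *That this outcome carries the trial's case on resistance and cost.* Resistance appears as background, and costs are a separate secondary outcome with their own analysis.

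**Conclusion.** The point holds as a minor one. The stated method for antibiotic days leaves out a recorded baseline variable that is likely to predict the outcome and that minimisation does not balance. The loss is in precision and in protection against chance imbalance; the validity of the comparison is not in doubt.

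The gain from adjustment runs from negligible to useful, depending on an entry effect that the documents do not give. Over the assumed range it is worth between about 8 and 167 extra patients' information on a trial of 500 (508 − 500 and 667 − 500). The calculation also assumes that the general ICU prevalence carries over to trial entrants, and it uses a comparison of means; a rank analysis would give somewhat different figures.

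**What to change.** Add one sentence to Data analysis. Days of antibiotic usage will be compared between randomised groups by a regression adjusted for antibiotics or anti-infectives at recruitment (yes/no) and the minimisation factors, on a transformed scale if needed. If the distribution is too skewed for that, a rank test stratified on entry antibiotic use will be used. The unadjusted comparison will be reported as supporting.

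State the rule for choosing between the two before outcome data are examined by arm. The study statistician supplies the confidential interim analyses, so the wording is best agreed by people who remain blinded to them.

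The cost is one sentence and a little analysis work. No extra patients or data items are needed. Writing it down beforehand also avoids a post-hoc decision about adjustment if an imbalance does appear.
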